# The effects of isolated ankle strengthening and functional balance training on strength, running mechanics, postural control and injury prevention in novice runners: design of a randomized controlled trial

**DOI:** 10.1186/1471-2474-15-407

**Published:** 2014-12-04

**Keywords:** Prevention, Running injury, Ankle strength, Neuromuscular training, Exercise intervention, Randomized controlled trial

## Abstract

**Background:**

Risk factors have been proposed for running injuries including (a) reduced muscular strength, (b) excessive joint movements and (c) excessive joint moments in the frontal and transverse planes. To date, many running injury prevention programs have focused on a “top down” approach to strengthen the hip musculature in the attempt to reduce movements and moments at the hip, knee, and/or ankle joints. However, running mechanics did not change when hip muscle strength increased. It could be speculated that emphasis should be placed on increasing the strength of the ankle joint for a “ground up” approach. Strengthening of the large and small muscles crossing the ankle joint is assumed to change the force distribution for these muscles and to increase the use of smaller muscles. This would be associated with a reduction of joint and insertion forces, which could have a beneficial effect on injury prevention. However, training of the ankle joint as an injury prevention strategy has not been studied. Ankle strengthening techniques include isolated strengthening or movement-related strengthening such as functional balance training. There is little knowledge about the efficacy of such training programs on strength alteration, gait or injury reduction.

**Methods/Design:**

Novice runners will be randomly assigned to one of three groups: an isolated ankle strengthening group (strength, n = 40), a functional balance training group (balance, n = 40) or an activity-matched control group (control, n = 40). Isokinetic strength will be measured using a Biodex System 3 dynamometer. Running kinematics and kinetics will be assessed using 3D motion analysis and a force platform. Postural control will be assessed by quantifying the magnitude and temporal structure of the center of pressure trace during single leg stance on a force platform. The change pre- and post-training in isokinetic strength, running mechanics, and postural control variables will be compared following the interventions. Injuries rates will be compared between groups over 6 months.

**Discussion:**

Avoiding injury will allow individuals to enjoy the benefits of participating in aerobic activities and reduce the healthcare costs associated with running injuries.

**Trial registration:**

Current Controlled TrialNCT01900262.

**Electronic supplementary material:**

The online version of this article (doi:10.1186/1471-2474-15-407) contains supplementary material, which is available to authorized users.

## Background

In the 1960s, research started to demonstrate a strong relationship between physical inactivity and a variety of diseases and health conditions, including coronary heart disease, hypertension, obesity and osteoporosis. Several studies found that participation in regular aerobic exercise does in fact reduce the risk of suffering from such conditions[1–6]. With the increasing awareness of the benefits of physical activity, a more health conscious general population expressed interest in exercise. Recreational running, with its accessibility and low monetary cost, has grown increasingly popular among the general population as a primary form of exercise[7]. However, the increase in popularity of running has also led to an increase in running-related injuries. Previous retrospective and prospective running injury studies have found the yearly injury incidence proportion to range from 26-85%[8–13]. The effects of running injuries include short-term and long term pain and discomfort. Short-term pain and discomfort would be due to the immediate effects of the injury. Long term effects may include a reduction of physical activity, osteoarthritis following acute injury, and increased health care costs[14, 15]. This highlights the impetus for further investigation into running injury prevention, as this is a growing concern for the general population not only from a running injury perspective, but also from a health standpoint.

A variety of intrinsic risk factors that are inherent to the runner have been identified for running injury. Some of the most commonly studied intrinsic variables include muscle strength and joint kinematics and kinetics during running[16–18].

### Muscle strength

It has been found that weak plantar flexor strength is associated with an increased incidence of Achilles tendinopathy, one of the most common overuse running injuries[16]. Furthermore, decreased muscular strength, particularly at the quadriceps and hamstrings, has been associated with increased incidence of patellofemoral pain syndrome, another common overuse running injury[17]. Reduced hip abduction strength has also been found in subjects suffering from patellofemoral pain syndrome and has generally been found to be a strong predictor of lower extremity injury risk[19, 20].

### Joint kinematics and kinetics

Research examining joint kinematic and kinetic variables during running has found that increased hip adduction and knee internal rotation are risk factors for the development of iliotibial band syndrome in runners[18]. Furthermore, it is thought that abnormal movement of the tibia and femur in the frontal and transverse planes affect patellar tracking and, therefore, increase the risk of suffering from patellofemoral pain syndrome[21]. This has been seen in runners with patellofemoral pain syndrome who demonstrated increased ankle eversion velocities and altered joint coupling mechanics[22]. It also has been found that runners with patellofemoral pain demonstrate increased knee joint angular impulse in the frontal plane compared to healthy runners[23].

Most of the recent running injury prevention studies have focused on hip strengthening protocols with the hope of reducing excessive joint movements and moments[24, 25]. The strengthening of the hip joint musculature assumes a “top down” approach where it is thought that improving strength at the hip will not only reduce movements and loading at the hip, but also at the more distal knee and ankle joints[26–28]. However, hip strengthening protocol interventions demonstrated that an increase in hip muscular strength was not accompanied by a reduction in excessive joint movements or moments in the frontal and transverse planes during running[24]. One potential explanation for these findings would be that the strengthening protocols were focusing on the proximal hip joint. It may be that a “ground up” approach should be used, in which specific ankle strengthening would be the primary focus of training. Such an approach would hypothesize that changes at the ankle joint will influence the mechanics of the more proximal knee and hip joints[27, 29]. Biomechanical injury prevention models focus on adjusting both the external and internal loads on the body[30]. In this sense, interventions aim to reduce the loads below the injury threshold or increase the body’s ability to tolerate the load[30]. It has been proposed that isolated ankle strengthening increases the strength of the small muscles surrounding the ankle joints, which are more adept for making quick postural adjustments without excessive force[31]. The use of these small stabilizing muscles rather than the larger muscles with longer lever arms may increase joint stability and reduce the loading at the joint and insertions of the larger muscles surrounding the ankle joint[31]. As a result, increased ankle musculature strength may not only increase the body’s ability to tolerate the load through an increased muscle ultimate strength but may also reduce the internal loads at the joint and at the muscle insertions below the injury threshold[31].

Another potential explanation for the lack of kinematic and kinetic changes found with hip musculature strengthening may be that the strengthening protocols used were not functional for an activity such as running. The principle of specificity dictates that training protocols should mimic the movements of the particular sport as closely as possible in order for the body to adapt appropriately[32]. Clinicians accept the importance of functional training and incorporate functional movements into training protocols, however there is a paucity of literature evaluating such functional training programs[33, 34]. Some hip strengthening protocols primarily focus on open chain, non-weight bearing exercises to strengthen the hip and thigh musculature[24]. Running is a closed chain, weight-bearing exercise and, therefore, training that does not incorporate similar mechanics that replicate the running movement may not alter running kinematics and kinetics. The only closed chain, weight-bearing exercise used by Willy and Davis was the single leg squat movement re-education protocol. The only movement differences found were those during the single-leg squat rather than during running. Similar results have been found previously indicating that isolated strengthening programs may not affect movement mechanics[35]. In order to alter lower extremity movement mechanics, training protocols may need to incorporate functional movements in order to improve neuromuscular control at the joint.

One form of training that may be able to accomplish this functional requirement is the incorporation of an unstable device into the training protocol. The appropriate training program using an unstable device should be able to incorporate functional closed chain, weight-bearing exercises that replicate the running movement to possibly increase strength and reduce excessive joint movements and moments during running. Functional balance training has traditionally been used in ankle injury rehabilitation programs with patients suffering from chronic ankle instability and repeated ankle sprains[36, 37]. One main goal of rehabilitation programs was to increase the strength of the ankle joint following injury. Research examining the effects of such training on lower extremity strength has shown successful increases in muscle strength[38, 39]. In recent years, functional balance training protocols have been utilized for the prevention of lower extremity injury in sport for healthy, physically active participants. Multifaceted training programs have seen positive results with respect to the reduction of excessive joint movements and moments as well as the incidence of acute and overuse lower extremity injuries in sport[40–42]. The same group that had utilized a multifaceted training program to reduce knee valgus in high school athletes went on to investigate the effects of the balance training portion of their protocol on knee valgus during landing[43]. For the same duration and intensity of training that was used in the multifaceted approach, it was found that balance training alone reduced hip adduction and ankle eversion angles during landing from a drop vertical jump. Similar results have been found in other functional balance training programs where frontal and transverse plane movements and joint moments have successfully been reduced. Even more importantly, functional balance training has successfully reduced the incidence of acute and overuse injuries in sports such as soccer, volleyball and basketball where non-contact ACL injuries and patellofemoral pain syndrome are common[42, 44–50]. However, such an intervention has yet to be evaluated in a recreational running setting.

#### Rationale

In summary, recreational running has grown in popularity as a form of aerobic exercise. Despite the health benefits associated with running, this steep increase in participation has inevitably led to an increase in the quantity of running injuries. Intrinsic risk factors have been associated with an increased risk of suffering from injuries, including reduced muscular strength and excessive lower extremity joint movements and joint moments in the transverse and frontal planes. Current injury prevention methods have focused on strengthening the hip and thigh musculature in the hopes of reducing excessive joint movements and moments. However, these strengthening interventions have not been successful for influencing running kinematics and kinetics and have yet to be tested in a prospective injury analysis. One potential reason for the lack of success with altering movement mechanics may be that the strengthening protocols are focusing primarily on the proximal joint. Another possible explanation is that the strengthening protocols were not functional for running, and thus, did not impact movement mechanics. Therefore, the purpose of this study is to compare the effects of isolated ankle joint strengthening and functional balance training with an activity-matched control group on lower extremity strength, running mechanics, postural control and the incidence of injury in healthy novice runners.

#### Objectives

To compare changes in (1) ankle, knee, and hip isokinetic strength, (2) lower extremity running kinetics and kinematics, and (3) postural control in healthy adult novice runners participating in an 8-week isolated ankle strengthening program or an 8-week functional balance training group to an activity-matched control group. Additionally, (4) injury rates in healthy adult novice runners participating in an 8-week isolated ankle strengthening program or an 8-week functional balance training group will be compared to those in an activity-matched control group.

#### Hypotheses

All hypotheses are made based on comparisons between each of the training groups and the control group.Isolated ankle strengthening will increase ankle isokinetic strength but not strength at the knee or hip joints.Isolated ankle strengthening will significantly decrease joint movements and joint moments in the frontal and transverse planes at the ankle during over ground and treadmill running.Functional balance training will significantly increase ankle and knee and hip isokinetic strength.Functional balance training will significantly decrease joint movements and joint moments in the frontal and sagittal planes at the ankle, knee and hip joints during over ground and treadmill running.Functional balance training will significantly reduce the center of pressure movement magnitude, increase the regularity of the center of pressure time series and improve performance on the Star Excursion Balance Test.Injury rates will be lower for the functional balance training group and the isolated ankle strengthening group compared to the activity matched control group.

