#### Analysis

Descriptive statistics of baseline characteristics of the participants in each group will be reported (mean, standard deviation, 95% confidence intervals). These will be presented in tabular form in order to determine if the groups were well balanced with respect to age, mass, height, weekly mileage and running experience[76].

For the isokinetic strength measurements, the peak torque of the three maximal isokinetic contractions will be identified. For postural control, the average entropic half-life in the medio-lateral and anterior-posterior direction will be calculated for the eyes open and eyes closed single limb tasks in the ML and AP direction. Additionally, the average COP 95% ellipse area, average COP path length, and average SEBT reach distance will be calculated. For the over ground running trials, a discrete analysis will be completed using Kintrak software (Human Performance Laboratory, Calgary, Canada) to calculate three-dimensional joint angular displacements, and moments for the ankle, knee and hip joints. Specifically, peak ankle eversion/inversion angle and moment, peak knee ab/adduction angle and moment, peak knee internal/external rotation angle and moment, peak hip ab/adduction angle and moment and peak hip internal/external rotation angle and moment during the stance phase will be calculated. All variables will be normalized to the stance phase of the right foot where heel contact and toe off will be identified as crossing a 15 N threshold. Additionally, a vector-based analysis approach (iterative support vector machine [SVM]) will be used to determine the classification rate of subjects following training as well as to identify the movements that have changed following training using the entire data set rather than discrete time points for the treadmill run[77]. A multivariate linear regression will be used to determine whether the change from baseline to the end of training in each variable for each training group is significantly different from the change found in the control group while controlling for age, gender, and any other baseline differences between the groups.

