Acute and overuse injury rates will be quantified separately due to the difference in injury definition[78]. Injury rates (number of injuries/1000 running hours) and 95% confidence intervals will be estimated. In an attempt to avoid the effects of dropout and adherence, an intent-to-treat analysis will be used. A multivariate Poisson regression analysis will be used to estimate incidence rate ratio (IRR) between the functional balance training group and the control group as well as between the isolated ankle strengthening group and the control group while controlling for age, gender and any other differences in baseline characteristics. Descriptive statistics for the amount of time missed from running due to injury (mean and standard deviation) will be calculated for both groups[79].

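### The hypotheses predict that balance training raises knee and hip strength and isolated ankle training does not, but the plan compares each arm only with control, which tests neither a difference between the programmes nor an absence of effect

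*Protocol article*

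**What the plan says.** The Hypotheses section of the protocol article opens by fixing the frame: "All hypotheses are made based on comparisons between each of the training groups and the control group". Within it, two hypotheses on isokinetic strength give different patterns for the two training arms:

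- Isolated arm: "Isolated ankle strengthening will increase ankle isokinetic strength but not strength at the knee or hip joints".
- Balance arm: "Functional balance training will significantly increase ankle and knee and hip isokinetic strength".

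The Analysis section keeps the frame. For the continuous outcomes, a regression asks whether the change "in each variable for each training group is significantly different from the change found in the control group". For injuries, the rate ratios are "between the functional balance training group and the control group as well as between the isolated ankle strengthening group and the control group". The Objectives and the Sample size section are also worded as training group against control. No section plans a comparison of the two training arms. None gives an equivalence margin or an interval-based rule for judging the predicted absence of a knee or hip strength effect.

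**The concern.** Read together, the two strength hypotheses say that the programmes act differently at the knee and hip. Under the stated plan, the only result that could support this is a significant balance-versus-control difference next to a non-significant isolated-versus-control difference. Two inferences would rest on that result, and neither is sound.

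- **That the programmes differ.** One significant and one non-significant comparison with a shared control is not a test of the difference between them. Two equally effective programmes will often split this way.
- **That isolated training has no knee or hip strength effect.** A non-significant result shows absence only if its interval excludes effects that matter. At this sample size the interval is wide.

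At stake is a published statement that only one programme builds proximal strength, when the data may not distinguish the two.

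**Working it through.** **Inputs.** From the Sample size section: effect size 0.71 (change in 95% ellipse area, training against control), power 80%, alpha 0.05, 32 per group, 20% dropout, 40 recruited per group. From Randomization procedure: allocation 1:1:1. Assumed: equal SDs, two-sided tests, and true effects of 0.3 and 0.5 SD, because the article gives no effect size for knee or hip strength.

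**1. The plan's own figure.** n = 2(1.960 + 0.842)² / 0.71² = 15.70 / 0.504 = 31.1, so 32 per group. 32 / (1 − 0.20) = 40. Both stated figures reproduce with a two-sided test; a one-sided test would give 25.

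**2. Chance of each comparison being significant.** With 32 per arm, the standard error of a difference is √(2/32) = 0.25 SD. The test statistic against control has mean d / 0.25 = 4d, and the two statistics are correlated 0.5 through the shared control. The chance of significance in the right direction is Φ(4d − 1.96):

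- d = 0.30: Φ(−0.76) = 22%
- d = 0.50: Φ(0.04) = 52%
- d = 0.71: Φ(0.88) = 81%

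**3. Discordant results when both programmes have the same true effect** (simulation, 400,000 replicates, 32 per arm):

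| True effect in both arms | Balance significant, isolated not | Either discordant pattern | Direct contrast significant | Direct contrast significant, given balance-only pattern |
|---|---|---|---|---|
| 0.30 SD | 12.1% | 24.2% | 5.0% | 13.6% |
| 0.50 SD | 16.6% | 33.3% | 5.0% | 12.2% |
| 0.71 SD | 11.0% | 21.9% | 5.0% | 14.2% |

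These rates are per variable. The Isokinetic strength section lists knee flexion and extension and hip abduction and adduction, so four variables are exposed. With 40 per arm (no dropout) the balance-only rates are 13.5%, 15.9% and 7.4%.

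**4. Unequal effects.** If the isolated effect is half the balance effect (0.355 against 0.71 SD), the balance-only pattern appears in 53% of trials, although isolated training does work. If the hypotheses are exactly true (0 against 0.71 SD), the pattern appears in 78%, and the direct contrast is significant in 81%.

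**5. Can non-significance show no effect?** The 95% half-width, unadjusted, is 1.986 × 0.25 = 0.50 SD (t on 93 df). An observed isolated-versus-control difference of exactly zero still allows an effect of up to 0.50 SD, which is 0.50 / 0.71 = 70% of the design effect. A non-significant estimate just below 0.50 SD has an upper limit near 1.0 SD.

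**6. What the direct contrast can do.** Its power at 32 per arm is 81% for a difference of 0.71 SD, 52% for 0.50 SD and 30% for 0.355 SD.

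**The case against.** The strongest reply is that comparison with control is a legitimate choice, held consistently from the purpose through to the injury analysis, and that the article never says it will declare one programme different from the other. That stands: a reader might infer that the protocol commits the error, but it contains no such conclusion and no rule for drawing one. What it does contain is a pair of strength predictions that its own comparisons cannot assess. An analysis plan might add the contrast, but a protocol that confines all its hypotheses to comparisons with control gives it no reason to.

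Two stronger readings are tempting and are not supported.

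- **That the same gap affects knee and hip mechanics.** The balance hypothesis on mechanics covers movements and moments "at the ankle, knee and hip joints during over ground and treadmill running". The isolated-arm hypothesis names the ankle and is silent on the knee and hip. The Background expects ankle changes to carry upward to those joints. The two mechanics hypotheses also name different planes. No predicted difference at the knee or hip is stated there.
- **That the direct contrast would separate two explanations for earlier failures.** The article does say "In order to alter lower extremity movement mechanics, training protocols may need to incorporate functional movements", and the Rationale adds "Another possible explanation is that the strengthening protocols were not functional for running, and thus, did not impact movement mechanics". It offers this beside the proximal-focus explanation and does not call the two mutually exclusive. The arms also differ in which joints are exercised: the balance routine has lunges, squats, hops and jumps, while the other arm isolates the ankle with elastic bands. A difference at the knee or hip would mix these features.

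Two further objections stand as limits. The rates in step 3 are conditional on equal effects, which the hypotheses do not predict. The direct contrast will also often be inconclusive. That is a reason to report its interval, not to infer a difference from discordant p-values.

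**Conclusion.** The point holds for knee and hip isokinetic strength. The predicted pattern could be supported only by one significant and one non-significant comparison with control. If the programmes are in truth equally effective, that pattern still appears in about 12%, 17% and 11% of trials per variable at 0.3, 0.5 and 0.71 SD. Non-significance in the isolated arm cannot establish the predicted absence of effect, because the interval extends about 0.50 SD either side.

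These figures assume 32 evaluable per arm, equal SDs, two-sided 0.05 and no covariate adjustment. Only 0.71 SD comes from the document, and it belongs to ellipse area. This is a gap in what the planned comparisons can support. It is not a numerical error or a contradiction, and it does not affect the validity of the comparisons with control.

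**What to change.** In the Analysis section, for knee and hip isokinetic strength:

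1. Add a balance-minus-isolated contrast with its 95% confidence interval, from the regression already planned, and label it secondary.
2. Judge the prediction of no knee or hip strength gain from isolated training by the isolated-versus-control estimate and its 95% interval, not by non-significance.
3. State that any claim that the programmes differ will rest on the direct contrast; otherwise state that no between-programme conclusion will be drawn.

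Adjust the opening sentence of the Hypotheses section to allow for this contrast. Settle the wording before results are seen.

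The cost is one further contrast for each of four strength variables and a few sentences. No new subjects, data or model are needed. The drawback is a few more secondary estimates, some of which will be inconclusive at a half-width of about 0.50 SD.
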